### Implementation of the leader resilience training program

2.2

The comprehensive framework for leader training includes a curriculum with 18 subcategories derived from the three multidisciplinary core components, covering a wide range of adaptation opportunities. The program is divided into two parts: Part I includes 18 basic training sessions, and Part II comprises 18 advanced sessions, totaling 36 pre-designed training sessions. This division ensures a progressive approach and macro program flexibility, as demonstrated in previous studies (Ungar and Jefferies, 2021; Las Hayas et al., 2019). To tailor the curriculum to the specific needs of participant organizations, a co-creation process will be employed. This involves collaboration with participant organizations to align the training program with their local visions and resilience needs. The selection of the final curriculum will be based on local aggregated baseline assessment data and will follow specific workshop protocols. The contextualized curricula will consist of 20 weekly one-hour resilience training sessions (embedded in weekly resilience-sprints), with 10 sessions in each part (Part I and Part II). Recognizing that resilience development requires time and effort, the program is designed as a prolonged training intervention, emphasizing reflection and experiential engagement in fostering resilience (Masten, 2011; Elkington and Breen, 2015; Cooper et al., 2013).

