The program will be implemented as a multi-level supportive initiative, incorporating resources from individuals, leader colleagues, HR, and management in participant organizations. We believe the integration of trained internal HR facilitators and co-creation of the curriculum increases ecological validity and implementation potential. The responsibility for resilience should be shared among stakeholders (Ungar and Jefferies, 2021), and our community-based approach integrates both individual and organizational resilience promoting factors identified within leader contexts (Förster and Duchek, 2017; Ukhova, 2020). For instance, the internal HR-resilience trainers will also undergo intensive resilience training themselves following specific educational protocols. This ensures that trainers are well-prepared and understand the program from a participant’s perspective before implementing the resilience training within their organization. The goal is to ensure an ethical and sustainable supportive learning environment for leaders. During implementation, we will use a unique method that we in this study term “intelligent psychological resilience training” to address the paradox of psychological leader resilience. This approach draws inspiration from community-based programs promoting individual physical health in organizational contexts (Sjøgaard et al., 2014; Dalager et al., 2016). This method underscores the importance of incorporating the two core components of resilience: adversity exposure and positive adaptation, tailored specifically to the individual. These components play a crucial role in building resilience capacity in training programs where challenges and adversity are needed (Vanhove et al., 2016). Exposure to moderate adversity is associated with resilience when facing controlled stressors and creating coping-related benefits (Seery et al., 2013). Therefore, participants will receive adversity-infused training in navigating and adapting to challenges based on their own selected and listed adverse experiences from the leader context to ensure ecological validity. This training will align specific exposure levels within the program’s scope and consider how participants perceive paradoxes and tensions differently (Lewis and Smith, 2023). Participants will be guided to set individual weekly learning attentions and goals to engage in self-directed learning processes between sessions (Knowles, 1980). They will be encouraged to apply resilience skills and behaviors in their leadership context and then discuss and evaluate the outcomes of various resilience strategies with HR-trainers and colleagues from the training community in subsequent sessions. This peer exchange is critical for leader resilience in organizational contexts (Förster and Duchek, 2017). Through an experiential-based approach (Kolb, 2014), the study thus aims to provide continuous and iterative learning opportunities for leaders, enabling them to apply resilience in interaction with natural environments when leading themselves and others through extreme times. Discussions will focus on cognitive, affective, and behavioral processes that constitute organizational leader resilience resources, integrating individual and organizational levels (Raetze et al., 2021). The longitudinal approach allows us to study the effects of resilience training over time, as recommended by previous reviewers (Robertson et al., 2015; Vanhove et al., 2016).

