### Randomization of participants

2.5

Following guidelines from a previous meta-review on resilience training in organizational contexts (Robertson et al., 2015), individual participants from organizational units will be randomly assigned to either the experimental or control group using computer-generated simple randomization. To mitigate contamination risks, the intervention group will from the beginning be advised not to share intervention content and training materials with the control group. HR-business partners will monitor the participating units, where leaders also work across the organization in many diverse team compositions, which we expect can reduce direct interaction, intervention conversations, and spill-over effects. Both groups will continue with their regular job responsibilities; however, the experimental group will also participate in weekly training sessions and additional self-directed training between sessions. The control group will only complete questionnaire measurements before, during, and after the intervention. After the final measurement, control group participants will be offered a condensed period of resilience training. This behavioral intervention study will be reported using an extension of the CONSORT Statement for social and psychological interventions (Montgomery et al., 2018).

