### Data management and statistical analysis of results

2.7

*A priori* power calculations were conducted using G*Power 3.1 (Faul et al., 2007) to determine the required sample size for a repeated measure and ANOVA assessing the interaction between time (three waves) and group (intervention versus control). The analysis for repeated measures, within-between interaction, was based on the following parameters: a medium Cohen’s effect size (*f* = 0.25), a significance (Alpha) level of 0.05, desired power of 0.08, and correlation among repeated measures of 0.5 for two groups and three measurements. The power analysis indicated that a total sample size of 28 participants (14 per group) was deemed necessary to achieve 80% power to detect a group x time interaction in this multi-wave organizational trial. Potential attrition across waves is accounted for as indicated in the CONSORT 2010 Flow Diagram in Figure 3, illustrating sample size planning for 30% attrition, assuming attrition occurs evenly from recruitment and across the waves with a rate of approximately 10% throughout the study. However, the aim is to increase the final target sample size to approximately 100 participants to enhance the validity of the study, due to pressures from extreme times in the organizations.

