**Figure 3 fig3:**
[figure not shown]
CONSORT flow diagram for attrition.

Propensity scores, calculated via logistic regression, will ensure balanced covariate distribution between intervention and control groups, enhancing the validity and reliability of the randomized controlled study (Rosenbaum and Rubin, 1983). Participants will complete secure online questionnaires via Survey X-act, collecting sociodemographic data (age, gender, education) job-related factors (function, seniority, occupation, responsibility, functional area), and outcome data. Aggregated local baseline assessments (T0) will guide need analysis and curriculum adjustments, as recommended by reviewers of leadership training, to optimize learning and transfer (Lacerenza et al., 2017). Internal HR-trainers will be blinded to subsequent intervention data (T1, T2) to minimize training biases. Growth modeling procedures in leadership training have proven effective in evaluating leader changes during interventions (Day et al., 2021). SAS PROC MIXED (SAS Institute Inc, 2022) will be used to fit the Growth Model. An unconditional model will predict longitudinal data, followed by conditional linear growth models examining interaction effects (*p*-values) of person-level covariates on short-term (T0, T1) and long-term (T0, T2) trajectories for all primary outcome variables. Rasch analysis will calculate Cronbach’s Alpha (reliability), item fit, eigenvalues (dimensionality), and differential item function (DIF). Process evaluation data will be analyzed using the package “Markov chain” (Spedicato, 2017) for discrete time Markov chains, examining the progression of Kirkpatrick levels and relevant resilience factors implemented over time. Descriptive analysis will be performed using R (R Core Team, 2024) to show influencing factors on the leader resilience training and resilience processes. Participant data from Survey X-act will be managed by a designated research team member using unique participant codes and analyzed by an external statistician to reduce research biases. Data retention is set for 5 years post-study.

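### Only the training arm is taught in groups, yet the power calculation and the model as described treat leaders as independent; if leaders trained together respond alike, type I error exceeds 5%

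*Protocol article*

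**What the plan says.** **Randomisation.** Section 2.5 states that "individual participants from organizational units will be randomly assigned to either the experimental or control group", by simple randomisation. The same section says controls do no more than complete the questionnaires at the three waves.

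**Delivery.** The Abstract describes 20 weekly collective training units. Section 2.2 gives these to internal HR trainers and has participants "discuss and evaluate the outcomes of various resilience strategies with HR-trainers and colleagues from the training community in subsequent sessions"; it regards this exchange between peers as critical. Content is set locally: "The selection of the final curriculum will be based on local aggregated baseline assessment data".

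**Power.** Section 2.7 lists the inputs of a repeated-measures, within-between interaction calculation: f = 0.25, "a significance (Alpha) level of 0.05", and "correlation among repeated measures of 0.5 for two groups and three measurements". The result is 28 participants (14 per group) for 80% power. A final target of about 100 is then mentioned; the reason given is validity under organisational pressure, not clustering.

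**Model.** Section 2.7 says "SAS PROC MIXED (SAS Institute Inc, 2022) will be used to fit the Growth Model", starting with an unconditional model and continuing with conditional linear growth models in which interactions with person-level covariates are examined. No training-group or trainer effect is named. Neither identifier is among the variables listed for collection.

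**The concern.** This is a partially nested design: individual randomisation, with one arm then treated in groups and the other left ungrouped. Shared trainers and peer learning are the intended mechanism, so the programme's own theory gives reason to expect leaders trained together to change in similar ways. A test that ignores such correlation counts the training arm as more information than it is. The standard error of the arm difference is then too small, p-values are too small, and the nominal 5% level is not kept. The same omission makes the stated power too high. The correlation of 0.5 in the power inputs does not help: it is between repeated measures on one leader, not between leaders in a group.

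**Working it through.** **Step 1. Reproduce the plan's figure.** Inputs from section 2.7: f = 0.25, alpha = 0.05, within-person correlation 0.5, 2 groups, 3 waves. The parameter list prints the power as 0.08, but the result sentence says 80%; 28 follows only from 0.80.

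Noncentrality = f² × N × 3 / (1 − 0.5). At N = 28 this is 0.0625 × 28 × 3 / 0.5 = 10.5, with df 2 and (28 − 2) × 2 = 52. Power is 81.2% at N = 28 and 79.5% at N = 27. The stated 28 reproduces, with no term for clustering.

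**Step 2. Let the training arm be clustered.** Let g be the training-group size and ICC the intraclass correlation of outcome change within a group. Both are assumed.

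- Training-arm design effect: D = 1 + (g − 1) × ICC.
- Variance ratio for the arm difference, 1:1 and controls unclustered: R = (D + 1) / 2.
- The correct standard error is √R times the naive one.
- Type I error of the naive two-sided test: 2 × P(Z > 1.96 / √R).
- Power: divide the noncentrality by R.

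Worked example, g = 7 and ICC 0.05: D = 1 + 6 × 0.05 = 1.30; R = 1.15; √R = 1.07; type I error 6.8%; noncentrality at N = 28 is 10.5 / 1.15 = 9.13, and power is 75%.

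| g | ICC | D | R | Type I error | Power, N = 28 | Power, N = 100 |
|---|---|---|---|---|---|---|
| 7 | 0.01 | 1.06 | 1.03 | 5.3% | 80% | >99% |
| 7 | 0.02 | 1.12 | 1.06 | 5.7% | 79% | >99% |
| 7 | 0.05 | 1.30 | 1.15 | 6.8% | 75% | >99% |
| 7 | 0.10 | 1.60 | 1.30 | 8.6% | 70% | >99% |
| 14 | 0.05 | 1.65 | 1.325 | 8.9% | 69% | >99% |
| 14 | 0.10 | 2.30 | 1.65 | 12.7% | 58% | 99% |
| 14 | 0.20 | 3.60 | 2.30 | 19.6% | 44% | 96% |
| 25 | 0.05 | 2.20 | 1.60 | 12.1% | not possible | 99% |
| 25 | 0.10 | 3.40 | 2.20 | 18.6% | not possible | 96% |

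The power columns keep the denominator df of the independent calculation, so with very few groups they are optimistic for an analysis that uses correct small-sample df.

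**Step 3. Check the type I error by simulation.** A t test on a change score, with no true effect and ICC 0.05, rejects in about 8% of simulated trials with 50 per arm in groups of 10, about 12% with 50 per arm in groups of 25, and about 9% with 14 per arm in one group. These agree with the formula.

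**Step 4. What a correct interval costs.** The ratio of interval widths is √R times the ratio of t quantiles, with Satterthwaite df for the clustered arm. At ICC 0.05:

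- 50 per arm, five groups of 10: about 11 df, interval about 1.2 times the naive width.
- 14 per arm, two groups of 7: about 3 df, about 1.7 times.
- 50 per arm, two groups of 25: about 2.1 df, about 2.6 times.

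**The case against.** **The model is not fully specified.** The article lists no random effects at all, not even one for the person. Naming person-level covariates says which interactions will be examined; it is not a complete specification. PROC MIXED can carry a group effect, and a statistical analysis plan that is not shown may add one. A reader might infer that the analysis model is definitely wrong; the document does not establish that. What stands is that the model as described has no training-group term and that the identifiers it would need are not among the listed data. The power calculation is a different matter: its inputs are all stated, and they contain no clustering.

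**The correlation may be small.** Number, size and stability of training groups are not given. Section 2.2 also describes individual content: self-chosen adverse experiences, personal weekly goals, self-directed learning. A low ICC is plausible, and at 0.01 with groups of 7 the standard error changes by 1.5%. A reader might infer that every interval will be too narrow; that holds only if the ICC is above zero.

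**Organisation is not the cause.** A reader might blame the missing organisation term and the locally chosen curriculum. Because leaders are randomised individually, organisation occurs in both arms; leaving it out puts its variance into the residual, which tends to widen intervals. A curriculum that differs between two organisations is a fixed difference in treatment, not a sampled cluster effect.

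**The larger target protects power.** Correct. A reader might infer that the trial is underpowered; at about 100 participants this does not follow for ICC up to 0.20 and groups up to 14. But a larger sample in groups of the same size does not lower the type I error, which depends on g and ICC.

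**Conclusion.** The point holds in conditional form. The figure of 28 rests on independent leaders, and the described model has nothing that would account for correlation within a training group. If that correlation is positive, a test that follows the text as written rejects too often: about 6% to 19% instead of 5% under assumed ICC 0.02 to 0.10 and groups of 7 to 25. The top of that range needs groups of 25 and ICC 0.10 together. The loss of power matters at the stated minimum of 28 (75% or 69% at ICC 0.05, for groups of 7 or one group of 14) and hardly at about 100. That the power calculation omits clustering is certain; that the model omits it is a reading of a condensed description; the size depends on two quantities that the document does not give.

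**What to change.** - Record training group and trainer for each participant in the training arm.
- State the planned number and size of training groups.
- If there are several groups, add a random effect for training group in the training arm only, with each control as a cluster of one, and use small-sample degrees of freedom (for example Kenward-Roger).
- If there are only one or two groups per organisation, the group variance cannot be estimated reliably; with one per organisation it cannot be separated from organisation at all. In that case report the treatment effect also with standard errors inflated for fixed ICCs, for example 0.05 and 0.10, as a sensitivity analysis.
- Restate power at 28 and at 100 participants over the same ICC range, and correct the printed power of 0.08.
- Organisation may be added as a fixed effect for precision, but this does not replace the steps above.

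The cost is analysis wording and the recording of group and trainer; treatment and recruitment need not change. Confidence intervals become wider: modestly with several groups (about 1.2 times for five groups of 10 at ICC 0.05), substantially with few (about 2.6 times for two groups of 25).

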**Figure 2 fig2:**
[figure not shown]
Overall framework for the leader resilience intervention.

### Research design

2.3

Consistent with recommendations from the latest comprehensive meta-review of resilience training in organizational contexts (Scheuch et al., 2021), this study is a randomized controlled trial (RCT) to examine the impact of behavioral resilience training in leader contexts. The majority of participants are recruited from the private organization, due to massive resource planning in the public organization. Following prior organizational resilience studies (Vanhove et al., 2016), we will assess primary outcomes to demonstrate resilience capacity (Britt et al., 2016) and evaluate dynamic resilience pathways over time (Masten and Reed, 2002), in this study through three measurements. Resilience in response to stressors of varying intensity is expected to show different outcome trajectories, allowing for more accurately observation and assessment in the context in which it occurs (Pangallo et al., 2015). To achieve this, participants will complete questionnaires at multiple time points: before (T0), during (T1), and after the intervention (T2). This longitudinal analysis will provide insights into resilience dynamics in leader settings and evaluate outcomes after the extended intervention, as suggested by several resilience researchers (Vanhove et al., 2016; Robertson et al., 2015; Ukhova, 2020). For secondary outcomes of interest, using a mixed-method design, we will assess training effects via the Kirkpatrick model (Kirkpatrick and Kirkpatrick, 2016), which also allows indirect analysis of the implemented resilience factors. Additionally, we will conduct a process evaluation of contextual conditions during and after the intervention (T1, T2) and explore participant experiences using various process evaluation frameworks proposed by intervention researchers (Moore et al., 2015; Randall et al., 2007; Braun and Clarke, 2006). The logical model for the framework variables and data sources used in the learning and development evaluation part of the study is mapped in Appendix 2. The overall aim is to evaluate the effects, processes and underlying mechanisms of the intervention, providing insights into what, why, and how of training psychological resilience in leader contexts. The total research design is outlined in Table 1 according to SPIRIT 2013 recommendations for standard protocols (Chan et al., 2013) showing different research and implementation activities.

**Table 1 tab1:** The schedule of enrolment, interventions, and assessments.

Study period							
	Enrolment	Allocation	Baseline	Intervention (Part I)	During	Intervention (Part II)	Follow-up (< 3 months)
TIMEPOINT		0	T0		T1		T2
ENROLMENT							
Eligibility screen							
Informed consent							
Allocation							
INTERVENTIONS							
Resilience training intervention (20 sprints)							
No intervention (control group)							
ASSESSMENTS							
Socio/ demographic variables: age, gender, education, job function, seniority, occupation, responsibility, functional area							
Primary outcome variables: Perceived stress, CD-RISC 10, RAW, WEMWBS, Flourishing							
Secondary outcome variables: training evaluation (Kirkpatrick x 20)							
Secondary outcome variables: process evaluation (self-constructed scales)							

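### Table 1 schedules allocation before the T0 baseline, and nothing says leaders stay unaware of their arm until T0 is complete, so self-reported baselines are open to bias

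*Protocol article*

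**What the plan says.** Table 1, which section 2.3 (Research design) presents as the overall design in SPIRIT format, gives allocation and baseline a column each, in the order "Allocation Baseline Intervention (Part I". The timepoint row reads "TIMEPOINT 0 T0 T1 T2": 0 belongs to allocation and T0 to the baseline column after it.

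The text of section 2.3 places T0 relative to the training only: "participants will complete questionnaires at multiple time points: before (T0), during (T1), and after the intervention (T2". It does not place T0 relative to randomization.

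Section 2.5 (Randomization of participants) says that individual leaders are "randomly assigned to either the experimental or control group using computer-generated simple randomization". It does not say when they are told the result. On the control arm it says: "The control group will only complete questionnaire measurements before, during, and after the intervention".

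The only blinding of people to data is in section 2.7: "Internal HR-trainers will be blinded to subsequent intervention data (T1, T2) to minimize training biases". That section also bases the growth models for all primary outcomes on two trajectories, T0 to T1 and T0 to T2.

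**The concern.** A baseline is safe from knowledge of the arm if it is collected before anyone can know the arm. The printed schedule gives up that protection, and no other safeguard is stated.

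Three features of this trial make the order matter:

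- **The arms are obvious once disclosed.** One group attends weekly sessions. The other answers questionnaires and is offered a condensed training after the last measurement.
- **All five primary outcomes are self-reported.** They cover stress, resilience and well-being (section 2.6.2). The leaders volunteered for the training (section 2.4), so being given a place or being told to wait could plausibly alter how they answer.
- **T0 enters every primary comparison.** A shift at T0 caused by knowing the arm would appear in the analysis as a difference in change, and the data could not separate it from a training effect.

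The direction is open. If leaders told to wait report worse at T0 and then settle back, the training looks weaker than it is. If leaders given a place report more strain at T0, it looks stronger.

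**Working it through.** **Step 1: the order of events.** Set side by side, Table 1 puts allocation in an earlier column than T0, section 2.3 requires only that T0 precede the training, and section 2.5 gives no date of disclosure. The three statements are compatible, and none of them makes leaders answer T0 unaware of their arm.

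**Step 2: reproduce the plan's own figure.** Inputs from section 2.7 are f = 0.25, alpha = 0.05, correlation rho = 0.5, k = 2 groups, m = 3 waves and 80% power. (The section also prints a desired power of 0.08; the sample size of 28 matches 0.80.) For the within-between interaction:

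- noncentrality λ = N·m·f²/(1 − rho) = 28 × 3 × 0.0625 / 0.5 = 10.5
- df1 = (k − 1)(m − 1) = 2; df2 = (N − k)(m − 1) = 26 × 2 = 52
- power = 0.812, and 28 is the smallest even N that reaches 0.80.

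The stated total of 28 is reproduced, so the same test can be used for the illustration.

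**Step 3: effect of a T0 shift on the estimate.** Assume that knowing the arm moves T0 by d SD between the arms, that T1 and T2 are not moved, and that training has no effect. The documents give no value for d.

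- Difference in change from T0: 0 − d, so the bias has size d. For d = 0.1 to 0.2 it is 0.1 to 0.2 SD.
- With T0 as a covariate: bias of size rho·d = 0.5 × 0.1 to 0.5 × 0.2 = 0.05 to 0.10 SD.

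**Step 4: effect on the test.** A shift of d at T0 alone has deviations from its mean over the three waves of 2d/3, −d/3 and −d/3. Half of the shift falls on each side of the average of the two arms, so the sum of squares per person is (d²/4)(4/9 + 1/9 + 1/9) = d²/6. Hence λ = N·d²/(6(1 − rho)) = N·d²/3 at rho = 0.5. At N = 100 this is 0.33 for d = 0.1 and 1.33 for d = 0.2. Rejection rates of the nominal 5% test with no true effect:

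| Assumed d (SD) | N = 28 | N = 100 |
|---|---|---|
| 0 | 5.0% | 5.0% |
| 0.1 | 5.7% | 7.6% |
| 0.2 | 7.7% | 16.1% |
| 0.3 | 11.5% | 31.7% |

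The target of about 100 participants makes the distortion of the test larger, because a fixed bias is then tested with more precision.

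**Step 5: scale against the planning effect.** Suppose the arms differ from T0 by the same amount at T1 and T2. Setting 3f² = d²/6 gives d = f·√18 = 0.25 × 4.243 = 1.06 SD. A shift of 0.1 to 0.2 SD is then 0.1/1.06 to 0.2/1.06, or about 9% to 19% of the effect for which the trial was sized.

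**The case against.** The strongest reply is that generating an allocation is not the same as disclosing it. Bias needs leaders to be told their arm before T0 and to answer differently because of it, and the article documents neither. This stands, and it limits the point to an exposure.

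A reader might find proof of early disclosure in the sentence of section 2.5 that says "the intervention group will from the beginning be advised not to share intervention content and training materials with the control group". It does not support that. The sentence concerns contamination, and its starting point is undefined. The final local curriculum is chosen from baseline data: "Aggregated local baseline assessments (T0) will guide need analysis and curriculum adjustments". So the start of training, after T0, is at least as natural a reading. The sentence on the control group's questionnaires likewise lists what that group does and does not date when its members learn their arm.

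A reader might also infer that leaders will be lost between allocation and T0 unevenly by arm. Section 2.7 assumes even attrition across the study and gives nothing by arm, so this remains a possibility only. That T0 steers the curriculum has no bearing on a between-arm bias.

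Finally, the cell marks of Table 1 and the flow diagram in Figure 3 cannot be seen in the text at hand, and an article condenses the full protocol. This calls for some caution, but the column headings and timepoint labels are legible and fix an order. The point therefore rests on a stated sequence, not on missing detail.

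**Conclusion.** The concern holds as an avoidable exposure. As printed, allocation precedes T0, and no stated rule keeps leaders unaware of their arm until they have answered. Every primary comparison starts from that measurement.

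The documents do not support the stronger reading that changes from T0 are biased. If arms are withheld until T0 closes, or if knowing the arm does not alter the answers, d = 0 and there is no bias. Direction and size cannot be determined from the article.

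The illustrative figures are a bias of 0.1 to 0.2 SD in change from T0, about half that with baseline adjustment, and a false-positive rate of about 8–16% at N = 100. They rest on an assumed d of 0.1 to 0.2, a shift confined to T0, correlation 0.5 and no true effect. A shift that persisted equally at T1 and T2 would cancel in change from T0 (d − d = 0).

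Setting the same shift against a conventional 0.5 SD effect would suggest 20–40% of the effect, but that denominator is not in the protocol. Against the protocol's own planning effect the share is about 9–19%.

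**What to change.** Reorder Table 1 so that baseline precedes allocation, and state in section 2.5 that T0 is completed and closed for all consenting leaders before the randomization is run. If randomization has to come earlier for practical reasons, the minimum is a sentence saying that no allocation is disclosed to leaders until T0 is closed. If either is already the practice, a corrected table and one sentence are enough.

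The cost is a few days between the closing of T0 and disclosure. Sample size, outcomes and analysis model do not change.
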